## **Protocol Version**

Version 2.0 Date: 21-Dec-2021.

## **Funding**

This study was supported by grants from the National Natural Science Foundation of China (ID: 82172639), the Project of Invigorating Health Care through Science, Technology and Education, Jiangsu Provincial Key Medical Discipline (Laboratory) (ZDXKB2016014), Nanjing Drum Tower Hospital Clinical Research Special Funding Program (2023-LCYJ-MS-15), and the Sino-German Mobility Programme (M-0670), Jiangsu Province Capability Improvement Project through Science, Technology and Education, Jiangsu Provincial Medical Key Discipline (Laboratory) Cultivation Unit (JSDW202221).

### *1.2 Steering Committee*

1) Role: Provides overarching oversight, reviews protocol amendments, and resolves operational challenges.

### *1.3 Data and Safety Monitoring Board (DSMB)*

An independent DSMB will oversee participant safety, review interim analyses and ensure data integrity. The composing members are as follows:

[name]: Chair of the DSMB, unblinded to group allocation but excluded from outcome assessment and statistical analysis.

[name], PhD: Voting member of the DSMB, providing clinical expertise and input on participant safety.

[name]: Voting member of the DSMB, contributing to the evaluation of adverse events and safety monitoring.

[name]: Voting member of the DSMB, providing statistical expertise and analysis support for interim data reviews.

## **2.Introduction**

### *2.1 Background and Rationale*

Radical prostatectomy (RP) is a primary treatment for localized prostate cancer (PCa), offering high cancer-specific survival (CSS) at 10-year follow-up, but is associated with early post-prostatectomy urinary incontinence (UI) in 25-86% patients. UI severely impacts patients' quality of life, and existing therapies like pelvic muscle training (PFMT) and artificial urinary sphincters (AUS) exhibit limited efficacy or invasiveness.

Electroacupuncture (EA) combines neuromodulation and Traditional Chinese Medicine (TCM) theory, demonstrating promise in female stress UI but lacking evidence in males. A rigorous evaluation of EA's efficacy and safety in men, using a standardized sham-controlled design, is critical to inform clinical practice. A sham acupuncture protocol was selected to isolate EA's specific effects from nonspecific factors (e.g., placebo, patient-provider interaction). Flat-tip needles applied at sham acupoints mimic EA's tactile sensation without active stimulation, ensuring blinding validity. This approach aligns with recommendations from the Standards for Reporting Interventions in Clinical Trials of Acupuncture (STRICTA) guidelines.

### *2.2 Objective*

This prospective, single-blinded, randomized clinical trial was designed to assess the effectiveness of EA for the treatment of UI after RP.

### *2.3 Trial Design*

This study is a prospective, single-center, randomized, single-blinded, sham-controlled clinical trial designed to evaluate EA's efficacy and safety in men with post-RP UI. Participants are randomized (1:1) to receive either EA or sham EA for 6 weeks, with follow-up extending to 20 weeks post-randomization. Blinding is maintained for participants and outcome assessors, while acupuncturists are unblinded to ensure protocol adherence. The trial adheres to Consolidated Standards of Reporting Trials (CONSORT) guidelines to ensure methodological rigor and transparency.

## **3. Methods: Participants, Interventions and outcomes**

### *3.1 Study Setting*

This single-center trial is conducted at the Department of Urology, Nanjing Drum Tower Hospital, Affiliated Hospital of Medical School, Nanjing University, China, a tertiary care academic medical center with extensive experience in the treatment of prostate cancer and urinary incontinence. Data collection will be limited to this single center to ensure consistency in study procedures and interventions. All interventions, assessments, and follow-ups are performed in a standardized clinical research unit equipped with dedicated acupuncture rooms and urological rehabilitation facilities.

### *3.2 Eligibility Criteria*

#### 1) Inclusion Criteria

- (a) Localized prostate cancer (stage: cT1-cT2, N0, M0);
- (b) 4-6 weeks after robot-assisted RP (RARP);
- (c) Mean 24-h pad number  $\geq 2$ ;
- (d) Prostate-specific antigen (PSA) test below cured level 1 month after surgery;
- (e) Eastern Cooperative Oncology Group (ECOG) performance status of 0-1

#### 2) Exclusion Criteria

- (a) Any prior neoadjuvant hormonal therapy;
- (b) Any prior prostatic surgeries;
- (c) Any prior history of operation on pelvis;
- (d) History of incontinence before RP.

### 3.3 Interventions

The intervention report adheres to the Standards for Reporting Interventions in Clinical Trials of Acupuncture (STRICTA) guidelines.

#### 1) Experimental Group

Based on the principles of TCM acupuncture theory and neuroanatomical structures, the intervention in this study involves EA at specific acupoints. The selected acupuncture sites were bilateral Ciliao (BL32), Zhongliao (BL33) and Xialiao (BL34) acupoints on the Bladder Meridian, which are closely associated with the sacral micturition center and are located in the second, third and fourth sacral foramina, respectively (Figure 1).

Patients in the experimental group receive EA stimulation at these acupoints. After skin disinfection, sterile adhesive pads were placed on predetermined acupoints. Single-use, sterile acupuncture needles with a diameter of 0.30 mm and a length of 75mm will be used. The needles are inserted through the adhesive pads at specific angles: the angles between the needle shaft and the skin surface range from 45° to 65°, and the optimal angles between the needle shaft and the posterior midline of the body for needle insertion are BL34 (20-40)°, BL32 and BL33 (10-25)°. The optimal depths for electrostimulation vary from cranial to caudal, with depths of 35-55mm for BL32, 25-45mm for BL33, and 20-40 mm for BL 34. Following needle insertion, small, equal manipulations of twirling, lifting, and thrusting were performed on all needles to reach de qi, a complex sensation characterized by soreness, numbness, swelling, and heaviness. After de qi is achieved, the bilateral BL32 (anode) and BL33 (cathode) are connected to the SDZ-V type electronic acupuncture therapy device (Suzhou Medical Supplies Factory Co., Ltd.). A sparse-dense wave, with a frequency of 2Hz/15Hz, will be applied, and the current intensity was adjusted to the maximum tolerable level for the patient, with the needles retained for 30 minutes. Participants receive 3 treatment sessions per week (ideally every other day) for 6 consecutive weeks, 18 sessions in total.

#### 2) Control Group

Participants in the control group undergo identical preparation procedures, but utilize single-use, custom-made flat-tip acupuncture needles (0.30 mm diameter, 75 mm length) to penetrate the adhesive pads without skin puncture. The sham EA points are offset one cun (approximately 20 mm) laterally from the experimental group's points. No de qi manipulation will be performed, and the duration and frequency of current output will be the same as in the experimental group. The treatment course and intervals for the control group are consistent with those of the experimental group.

All participants are suggested to undergo PFMT as part of standardized postoperative care. In accordance with our institutional protocol, PFMT will be initiated after catheter removal, as recommended by AUA/SUFU guideline. Participants performed three sets of pelvic floor

muscle exercises daily, with each set consisting of 10 contractions held for 10 seconds each, with a 10-second rest between contractions.

### 3) Criteria for Discontinuing or Modifying Allocated Interventions

- (a) Participant withdrawal of consent
- (b) Severe adverse events (e.g. persistent pain, infection) requiring discontinuation
- (c) Disease progression necessitating alternative therapies.

### 4) Strategies to Improve Adherence

- (a) Reminder calls/notifications before each session.
- (b) Flexible scheduling to accommodate participant availability
- (c) Adherence monitoring via session attendance logs reviewed weekly by the study coordinator.

### 5) Permitted Concomitant Care and Prohibited Interventions

Analgesics (e.g. nonsteroidal anti-inflammatory drugs) are allowed for unrelated conditions but documented. Additional acupuncture, neuromodulation therapies, or surgical interventions for UI during the trial period is prohibited.

## 3.4 Outcomes

### 1) Primary Outcome

UC (define as the use of 0 to 1 pad per day) rate after the 6-week treatment period.

### 2) Secondary Outcomes

- (a) Changes in the amount of 24-h urine leakage at the end of 6-week treatment period compared with baseline.
- (b) Changes in the mean number of pads used daily at the end of 6-week treatment period compared with baseline.
- (c) Prostate-related symptoms assessed by changes in the Expanded Prostate Cancer Index Composite for Clinical Practice (EPIC-CP) UI score at the end of 6-week treatment period compared with baseline.
- (d) Time to UC recovery in weeks.

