### *3.7 Data Collection and Management*

Data collection will be conducted using standardized case report forms (CRFs). Baseline data include demographic information (age, body mass index [BMI]), medical history (history of hypertension, history of diabetes), unhealthy habits (smoking history, alcohol consumption), oncological features (preoperative PSA, biopsy International Society for Urological Pathology [ISUP] grade group, clinical T stage, Eastern Cooperative Oncology Group [ECOG] status, involvement of pelvic lymph node dissection [PLND], and nerve-sparing status), and initial UC status (number of pads used per day, 24-h pad weight, Expanded Prostate Cancer Index Composite for Clinical Practice [EPIC-CP] UI score). Outcome data will be collected after the 6-week intervention period, and at 12, 16, and 20 weeks post-randomization.

Data management is overseen by an independent DSMB composed of experienced clinical research coordinators and statisticians. The DSMB will ensure the accuracy, completeness, and confidentiality of all study data by conducting monthly comprehensive data checks to identify systematic errors or problems in data entry. Manual checks will be performed to identify more complex and less common errors. Any discrepancies or missing data will be flagged and resolved through communication with the study sites. Only authorized personnel will have access to the data and all data will be anonymized to protect participant confidentiality. Any requests for data access will be reviewed and approved by the DSMB.

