#### *2) Data Analysis Plan*

All analyses will be performed using the intention-to-treat (ITT) principle, including all randomized participants. Continuous variables are summarized using means with standard deviations (SD) or medians with interquartile ranges (IQR), as appropriate. Categorical variables are described using frequencies and percentages. For variables, Student t-tests or Mann-Whitney U tests are applied, depending on the data distribution. Chi-square tests are used for categorical variables, and Kruskal-Wallis tests are used for ordinal variables. Statistical analyses are conducted using SPSS software, version 21.0 or higher (IBM, USA) and R software (version 3.6.0 or higher).

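### Week-6 changes in pad weight, pad count and EPIC-CP are tested without baseline adjustment, and the test is chosen from the data; one prespecified ANCOVA would be at least as precise and would fix the effect measure

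*Protocol*

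**What the plan says.** Protocol section 3.4 (Secondary Outcomes) sets three quantitative measures as changes from baseline at the end of treatment:

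- (a) "Changes in the amount of 24-h urine leakage at the end of 6-week treatment period compared with baseline"
- (b) for pad count, in the same form: "Changes in the mean number of pads used daily at the end of 6-week treatment period compared with baseline"
- (c) the EPIC-CP measure, the change in "UI score at the end of 6-week treatment period compared with baseline"

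Outcome (d) is "Time to UC recovery in weeks". It rests on the continence definition in the primary outcome: "UC (define as the use of 0 to 1 pad per day) rate after the 6-week treatment period".

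The Data Analysis Plan in section 3.8 reads: "For variables, Student t-tests or Mann-Whitney U tests are applied, depending on the data distribution". The word that should qualify the variables is missing. The next sentence covers categorical and ordinal variables separately, so continuous variables are meant. No baseline covariate is named. If EPIC-CP were classed as ordinal, the stated method would be Kruskal-Wallis, which with two arms is again an unadjusted rank comparison.

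Section 3.7 lists pad count, 24-h pad weight and the EPIC-CP incontinence score among the baseline data. On later visits it says: "Outcome data will be collected after the 6-week intervention period, and at 12, 16, and 20 weeks post-randomization".

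**The concern.** Two features of the stated method can be improved at no cost.

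First, a change score subtracts the whole baseline value, which amounts to fixing the slope of week 6 on baseline at 1. When the true slope differs from 1, the comparison carries avoidable variance. It also moves with any chance difference in baseline between the arms. Section 3.6 describes a 1:1 sequence and mentions no stratification by baseline leakage, so some chance imbalance must be expected with about 50 men per arm.

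Second, a t-test compares means and a Mann-Whitney test compares ranks. If the observed distribution decides between them, the quantity to be reported for each outcome is unknown until the data are seen, and the three outcomes could end up on different measures.

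At stake are the precision and interpretability of the three quantitative secondary outcomes.

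**Working it through.** **The protocol's own figure.** Section 3.8 states 110 participants (55 per group) for continence rates of 20% and 48%, two-sided 0.05, 80% power and 10% dropout. With Fisher's exact test, 49 per arm gives 78.9% power and 50 per arm gives 80.1%; 50 x 1.10 = 55. The figure reproduces. It concerns the binary primary outcome, and no figure is stated for outcomes (a) to (c).

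**Precision.** Let r be the correlation between baseline and week 6, and k the week-6 SD divided by the baseline SD. Neither is in the protocol; both are assumed. Per unit of week-6 variance, the variance terms of the group difference are:

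- change score: 1 + 1/k² − 2r/k
- ANCOVA: 1 − r²

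At k = 1 these are 2(1 − r) and (1 − r)(1 + r), so the ratio is (1 + r)/2. The ANCOVA to change-score ratios are:

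| k | r = 0.3 | r = 0.5 | r = 0.7 | r = 0.9 |
|---|---|---|---|---|
| 0.7 | 0.417 | 0.465 | 0.490 | 0.405 |
| 1.0 | 0.650 | 0.750 | 0.850 | 0.950 |
| 1.3 | 0.805 | 0.912 | 0.991 | 0.917 |

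The two methods tie only when the baseline slope r x k equals 1. Otherwise ANCOVA has the smaller large-sample variance.

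**What this means for power.** Take 55 x 0.9 = 49.5 evaluable men per arm, k = 1, and an assumed true difference of 0.5 week-6 SD:

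- r = 0.3: 56% with the change score, 74% with ANCOVA
- r = 0.5: 70% and 82%
- r = 0.7: 90% and 94%

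**Chance imbalance.** If the arms differ by d at baseline, the change-score contrast is expected to move by (r x k − 1) x d. With 49.5 per arm, one standard error of the baseline difference is √(2/49.5) = 0.20 SD. At r = 0.5 and k = 1 the shift is (0.5 − 1) x 0.20 = −0.10 SD. ANCOVA estimates the slope instead of fixing it at 1, and so removes this shift. Averaged over randomisations d is zero, so the change-score comparison is unbiased.

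**Choosing the test from the data.** The protocol names no rule, so a Shapiro-Wilk pre-test in each arm was assumed. In 10,000 simulated null trials with 50 per arm, the type I error of the two-step procedure was 0.048 for normal data, 0.051 for lognormal data and 0.052 for skewed data with 20% zeros. The simulation error is about √(0.05 x 0.95/10,000) = 0.002, so none of these departs materially from 0.05.

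**The case against.** The strongest reply is that the analysis paragraph is a generic list, and that covariates and models are commonly left to a statistical analysis plan, which is not at hand. The outcome definitions do not forbid a baseline covariate. This stands in part: silence on a covariate alone would be no finding. But the protocol does more than stay silent. Under a heading for the analysis plan it names unadjusted tests and a data-dependent choice between them. If a separate plan already specifies an adjusted analysis, the two texts need to be reconciled.

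It can also be said that the gain is assumption-driven. That is true. Equal SDs are doubtful here, because entry requires at least 2 pads per day, which narrows the baseline spread of pad count, while recovery may narrow the week-6 spread. The direction of the precision result does not depend on this; its size does.

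A reader might infer more than the protocol supports:

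- *The week 12, 16 and 20 data go unused.* Continence is defined by pad count, and time to continence is outcome (d), so later pad counts do feed a stated outcome. For pad weight and EPIC-CP no stated outcome uses those visits. Week 6 is the end of treatment and a legitimate endpoint, so this is not an error in itself.
- *Picking the test from the data inflates false positives or is what loses precision.* The simulation shows no material inflation. The loss of precision comes from the unadjusted change score.
- *Fewer patients would be needed.* The sample size is set by the binary primary outcome, so the variance ratio has no bearing on N.
- *A repeated-measures model, a log transform and further continence-rate outcomes are required.* These are debatable additions. In particular, a difference in log(1 + grams) is not a clean ratio of leakage if dry men record 0 g.

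**Conclusion.** The point holds for secondary outcomes (a) to (c) only. The stated analysis is never more precise in large samples than one that uses baseline data already collected. Under equal SDs, ANCOVA has 65% to 85% of the change-score variance for r from 0.3 to 0.7. Over SD ratios of 0.7 to 1.3 and r from 0.3 to 0.9, the range is about 40% to 99%. The gain therefore runs from large to negligible, and the protocol gives nothing with which to narrow it.

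It would be wrong to call the change-score comparison biased without qualification. It is unbiased under randomisation. Given a chance imbalance it is shifted, over-correcting when the baseline slope is below 1, which at equal SDs means any r below 1. The data-dependent test is a weakness of prespecification: it leaves open whether a mean difference or a rank comparison will be reported.

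This is a worthwhile improvement to three secondary analyses. It does not threaten the primary result.

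**What to change.** Keep week 6 as the endpoint. For (a) to (c), replace the unadjusted tests with one prespecified ANCOVA: treatment arm plus the baseline value of the same measure. The outcome definitions can stay as they are, because ANCOVA on the change and on the week-6 value give the same treatment estimate.

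For skewed pad weight, fix a single approach in advance, such as a robust or a rank-based ANCOVA, and state the effect measure that goes with it. A robust ANCOVA keeps the result in grams; a rank-based one does not.

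Optionally, report pad weight, pad count and EPIC-CP at weeks 12, 16 and 20 from the same adjusted model, labelled as descriptive evidence on durability.

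The cost is a change of analysis wording on data already scheduled, with no added patients or visits. The primary outcome and N = 110 stay as they are.

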## 3.5 Participant Timeline

A detailed schedule of enrollment, randomization, intervention and follow-up is provided in Figure 2. The study involves a 6-week intervention period accompanied with a 20-week follow-up period. Participants will be assessed at baseline, at the end of the intervention period, and at 12, 16, and 20 weeks post-randomization.

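### Time to UC recovery is right-censored and seen only at visits, but the tests named in Protocol 3.8(2) do not handle censoring and no rule covers men who have not recovered or who drop out

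*Protocol*

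**What the plan says.** Section 3.4(2)(d) makes "Time to UC recovery in weeks" a secondary outcome. Continence itself is defined in the primary outcome: "UC (define as the use of 0 to 1 pad per day) rate after the 6-week treatment period".

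On timing, section 3.5 says "Participants will be assessed at baseline, at the end of the intervention period, and at 12, 16, and 20 weeks post-randomization", and section 3.7 agrees: "Outcome data will be collected after the 6-week intervention period, and at 12, 16, and 20 weeks post-randomization". Section 2.3 describes the trial "with follow-up extending to 20 weeks post-randomization". Section 3.5 also speaks of a "6-week intervention period accompanied with a 20-week follow-up period".

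On analysis, section 3.8(2) requires intention-to-treat analysis of every randomized participant and then lists the tests. The first sentence on tests reads "For variables, Student t-tests or Mann-Whitney U tests are applied, depending on the data distribution". The next assigns chi-square to categorical and Kruskal-Wallis to ordinal variables. No test is tied to a named outcome. The section gives no censoring rule and no value for a man who never reaches 0-1 pad per day.

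**The concern.** A man who is still incontinent at his last visit has no recovery time; it is known only to lie beyond that visit. A duration in weeks falls most naturally under the t or Mann-Whitney sentence, and neither test can take such a man as he stands. The analyst must then choose among three courses, and the protocol does not say which:

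- Drop him. This conflicts with analysing all randomized men, and it conditions on the outcome. If EA makes more men continent, that benefit disappears from the comparison.
- Enter his last week as if it were his recovery week. A man who drops out early then counts as an early recovery.
- Rank him behind everyone who recovered. This can be a valid test, but it has to be laid down in advance.

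The recovery week is also known only to within an interval. A man who becomes continent during treatment is first seen to be so at week 6, so mean or median weeks partly describe the visit schedule.

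**Working it through.** **The plan's own figure.** The protocol gives no figure for this outcome. Its sample size does reproduce: for 20% v 48%, two-sided 0.05, Fisher's exact test has power 0.789 at 49 and 0.801 at 50 per arm, and 50 x 1.1 = 55 per arm, 110 in total. I use this only to set the scale: about 50 evaluable men per arm.

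**How many men would be censored.** Assume that 20% and 48% are week-6 rates and that the recovery hazard is constant (the second assumption is not in the protocol).

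- Sham: rate = -ln(0.80)/6 = 0.0372 per week; not recovered at week 20 = exp(-20 x 0.0372) = 0.48.
- EA: rate = -ln(0.52)/6 = 0.1090 per week; not recovered at week 20 = exp(-20 x 0.1090) = 0.11.

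On these assumptions censoring is substantial and differs between arms even before any dropout.

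**Course 1 (drop) and course 3 (rank last), against log-rank.** Simulation with 50 per arm, visits at 6/12/16/20 weeks and no dropout; 4000 replicates, or 3000 for the ranked-last column. The curves are assumptions; only the 20% v 48% at week 6 in scenario C comes from the protocol.

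| Scenario | Sham, cumulative % | EA, cumulative % | Recovered men only, Mann-Whitney / t | Mann-Whitney, non-recovered last | Log-rank |
|---|---|---|---|---|---|
| A: same timing among recoverers | 20, 35, 44, 50 | 32, 56, 70.4, 80 | 0.045 / 0.047 | 0.79 | 0.87 |
| B: EA adds late recoveries | 20, 30, 36, 40 | 30, 50, 62, 70 | 0.075 / 0.074 | 0.73 | 0.83 |
| C: mainly early effect | 20, 38, 48, 55 | 48, 60, 67, 72 | 0.605 / 0.562 | 0.75 | 0.60 |

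Repeat runs moved these by a few hundredths at most.

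Scenario A can be checked by hand. Among recovered men the shares by visit are 0.40, 0.30, 0.18 and 0.12 in both arms (for example 0.20/0.50 and 0.32/0.80), so a test on recovered men has nothing to detect although 30 percentage points more men recover on EA.

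In scenario B the mean week among recovered men is:

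- EA: (6 x 0.30 + 12 x 0.20 + 16 x 0.12 + 20 x 0.08)/0.70 = 7.72/0.70 = 11.0.
- Sham: (6 x 0.20 + 12 x 0.10 + 16 x 0.06 + 20 x 0.04)/0.40 = 4.16/0.40 = 10.4.

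The better arm therefore looks slower.

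**Course 2 (last week used as recovery week).** Simulation with 55 per arm, 2000 replicates, the constant sham hazard above in both arms, and dropouts last seen at week 0, 6, 12 or 16 with equal chance (all assumptions). Type I error at nominal 0.05:

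| Dropout sham / EA | t | Mann-Whitney | Non-recovered last | Log-rank |
|---|---|---|---|---|
| 10% / 10% | 0.04 | 0.04 | 0.04 | 0.05 |
| 15% / 5% | 0.10 | 0.10 | 0.05 | 0.05 |
| 20% / 0% | 0.30 | 0.27 | 0.06 | 0.04 |

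With the two hazards above and 10% dropout per arm, power was 0.99 for log-rank, 0.98 for non-recovered last, 0.96 for either test on last week as recovery week, and 0.33 (t) or 0.31 (Mann-Whitney) on recovered men only.

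**The case against.** The strongest reply is that a reader might infer that the listed tests must give a wrong answer, and that this is not so. Mann-Whitney is on the list. With non-recovered men tied at the last rank and complete follow-up it holds its level (0.04 to 0.05 under the null) and has about 73-80% power. In scenario C, the one that uses the protocol's week-6 rates, it beats log-rank (0.75 v 0.60). The very low power figures arise only if men are dropped, which the protocol does not say will happen and which its intention-to-treat sentence argues against. They also rest on 20-week rates that are not in the documents. All of this stands. It shows that a listed test can be made to work by a rule, and the protocol does not state the rule.

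A second reply is that such detail belongs in the SAP, which is not shown and may name a survival method. This stands in part: nobody can conclude that the trial lacks a survival analysis. But section 3.8(2) does not leave the methods open. It states a list, and the list does not fit outcome (d).

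Two other inferences go too far. One is that nothing is recorded between visits. The text describes no pad record between visits, but Figure 2, which holds the detailed schedule, is not shown, and men attend three sessions a week during treatment. The other is that follow-up runs to 26 weeks (6 + 20). One phrase in 3.5 allows that reading, but the visit list in the same section ends at week 20, as do 2.3 and 3.7.

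**Conclusion.** The point holds in this form: outcome (d) is right-censored at week 20 and, on the text, observed only at four visits; the tests named in 3.8(2) do not handle censoring; and no rule covers non-recovered men or dropouts. The effect depends on the course the analyst takes. Dropping men costs nearly all power in scenarios A and B and little in scenario C. Entering the last week as the recovery week costs type I error control if dropout differs between arms. Ranking non-recovered men last costs little. These sizes rest on assumed recovery curves, hazards and dropout patterns; that the result depends on an unstated choice does not. The outcome is secondary, so neither the primary comparison nor the 110 participants is affected. The change should be made, but the trial's main conclusion does not depend on it.

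**What to change.** In 3.8(2), state that time to UC recovery is analysed in all randomized men by a grouped log-rank test or a discrete-time (complementary log-log) model over the intervals (0,6], (6,12], (12,16] and (16,20] weeks. Define recovery as the first visit with 0-1 pad per day, right-censor at the last attended visit, and report cumulative recovery by arm at each visit. In 3.5, align the wording on the length of follow-up with the 20 weeks from randomization in 2.3.

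The cost is a few sentences; no new data collection is needed. Estimates will refer to the visit grid rather than exact weeks. Log-rank can be less powerful than a ranked-last test if the effect is mainly early (0.60 v 0.75 in scenario C). A man with no visit after baseline is censored at time zero and adds no information, and censoring is assumed to be unrelated to recovery.
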